### 7.4 Fluconazole Dose Modifications

- - 1. Renal Impairment

The initial fluconazole dose will be given as specified, independent of the screening creatinine clearance. Subsequently, doses **of study-provided fluconazole** should be adjusted according to the table below for subjects with decreased creatinine clearance. **Dose adjustments to fluconazole that is given in combination with ampho B are also important; refer to the package insert for guidance.**

Table 7-1

| Creatinine Clearance  (Measured or Estimated) | Fluconazole Dose |
| --- | --- |
| ≥ 50 mL/min | current dose |
| 20 - 49 mL/min | 50% current dose |
| 0 – 19 mL/min | 25% current dose |

- - 1. Body Weight < 60 kg at Study Entry

The following adjustments should be made in the induction dose of fluconazole for participants whose weight at entry is < 60 kg. All adjusted doses of fluconazole should be rounded up to the nearest 200 mg, based on the participant’s actual weight. For example, if a participant in Cohort 1 weighs 42 kg, 42 kg X 20 mg/kg = 840 mg; dose should be rounded up to 1000 mg. Weight-based adjustments must NOT be made to any consolidation or maintenance doses of fluconazole.

Table 7-2

| Weight at Entry | Weight-Adjusted Daily Fluconazole Dose for Induction Step | | |
| --- | --- | --- | --- |
| For 1200 mg cohorts | For 1600 mg cohorts | For 2000 mg cohorts |
| < 60 kg | 20 mg/kg up to 1200 mg total | 26 mg/kg up to 1600 mg total | 33 mg/kg up to 2000 mg total |

### 7.5 Fluconazole-Induced Rash

Grade 1 or 2: Fluconazole should continue without interruption, at the discretion of the site investigator. Participants with a Grade 1 or 2 rash may be treated symptomatically with permitted antipyretic, antihistamine, and/or non-steroidal anti-inflammatory medications, but should be monitored closely by the site investigator.

Grade 3: Participants should interrupt fluconazole. If the Grade 3 rash is considered to be most likely due to concomitant illness or medication, standard management, including discontinuation of the likely causative agent, should be undertaken. If the rash resolves to Grade ≤ 1 within 3 days following an interruption, the investigator should consider whether re-starting fluconazole, as described in section 7.1, is appropriate.

Grade 4: In case of exfoliation, mucosal involvement, or target lesions (erythema multiforme), or any evidence of Stevens-Johnson syndrome or toxic epidermal necrolysis (TEN), participants should permanently discontinue fluconazole.

### 7.6 Adrenal Insufficiency (AI)

Fatigue, weakness, loss of appetite, nausea, and vomiting with orthostatic hypotension may be signs of secondary AI. It is unusual to have the low sodium and potassium levels that are frequently seen in primary AI. Causes of AI may be secondary to cryptococcal infection and typically resolve with treatment of the infection. However, AI may also be related to high doses of fluconazole. Participants who develop these symptoms while taking fluconazole may need further evaluation for secondary AI (eg, cortisol stimulation test, if available). Treatment with prednisone or a similar glucocorticosteroid may be indicated. Note that cortisol levels in samples collected early in the day tend to be less than 3 mcg/dL; ACTH levels are low in the setting of secondary AI.

### 7.7 Pregnancy

Women who become pregnant on study while receiving fluconazole must discontinue fluconazole immediately. The core team should be notified as soon as is reasonably possible.

If a woman has completed the study or chooses to discontinue from the study before the end of the pregnancy, then site staff should request permission to contact her regarding pregnancy outcomes at the end of pregnancy. If the information is obtained, pregnancy outcomes will be submitted on a CRF at the end of the pregnancy.

Pregnancies that occur on study in women who are taking ARVs will be reported prospectively to The Antiretroviral Pregnancy Registry. Intrapartum complications and/or pregnancy outcome will be recorded on the CRFs and also reported to The Antiretroviral Pregnancy Registry. More information is available at [www.apregistry.com](http://www.apregistry.com/). [contact]; [contact]. At sites outside the US, report pregnancies to The Antiretroviral Pregnancy Registry by Fax at: [contact], or by phone at: [contact].

## 8.0 CRITERIA FOR PREMATURE TREATMENT OR STUDY DISCONTINUATION

### 8.1 Treatment Discontinuation

- **Failure to have CM confirmed by Day 5 by testing performed at a DAIDS-approved laboratory**
- Fluconazole-related dose-limiting or ampho B-related treatment-limiting toxicity (see section 7.0, Clinical Management Issues or section 5.0, A5225/HiFLAC MOPS).
- Pregnancy or breast-feeding (for fluconazole).
- Interruption of oral fluconazole for any reason for more than 3 consecutive days.
- Requirement for prohibited concomitant medications (see current A5225/HiFLAC MOPS).
- Clinical reasons believed life threatening by the physician, even if not addressed in the clinical management section of the protocol.

### Study Discontinuation

- Negative screening CSF culture and/or confirmatory HIV status screening results

**A negative screening CSF culture is defined as**

- **a negative culture after 2 weeks of incubation even in the setting where the CSF antigen testing is positive by latex agglutination from a referring laboratory**

**or**

- **a negative culture after 5 days of incubation if there is no yeast found on culture and there is a negative CSF antigen test by the latex agglutination method by Day 5 from an approved laboratory.**.
- Failure to obtain a quantitative CSF culture at screening or entry.
- Failure to initiate study treatment within 72 hours after entry.
- Initiation of NVP prior to fluconazole dose reduction to ≤ 400 mg daily
- Request of the primary care provider if s/he thinks the study is no longer in the best interest of the participant.
- Failure by the participant to attend three consecutive clinic visits.
- Request by the participant to withdraw.
- Participant judged by the investigator to be at significant risk of failing to comply with the provisions of the protocol as to cause harm to self or seriously interfere with the validity of the study results.
- At the discretion of the Office for Human Research Protections (OHRP), Food and Drug Administration (FDA), NIAID, ACTG [including the Study Monitoring Committee (SMC)], local IRB/EC or other regulatory authority, industry supporter, or investigator.

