Based on these data, coadministration of these two drugs is discouraged in A5225/HiFLAC. Furthermore, coadministration of NVP and fluconazole at fluconazole doses > 400 mg daily is prohibited in A5225/HiFLAC. While the decision regarding coadministration of NVP and fluconazole at fluconazole doses of ≤ 400 mg fluconazole daily is left to the discretion of the treating clinician, we strongly urge the institution of weekly monitoring of hepatic enzymes [Manosuthi 2007].

Limited data on the coadministration of fluconazole and EFV have demonstrated a small increase in EFV exposures with no change in fluconazole concentrations. Beginning at week 4, EFV may be used concomitantly with fluconazole without regard to fluconazole dose.

When zidovudine (ZDV) is administered at 200 mg every 8 hours concomitantly with 400 mg fluconazole daily, Cmax and AUC of ZDV were increased 84.2%, and 74.4%, respectively [Sahai 1994]. Therefore, caution should be used when coadministering these two drugs.

Limited data on the drug interaction between RIF and fluconazole demonstrate enhanced metabolism of concurrently administered fluconazole, thereby reducing the AUC of fluconazole by 23% [Apseloff 1991]. Therefore, the use of RIF is prohibited for A5225/HiFLAC study participants receiving 1200 mg daily fluconazole. RIF may be initiated after these participants have initiated the consolidation dose of 600 mg fluconazole daily (rather than 400 mg daily) or the maintenance dose of 200 mg daily fluconazole. Coadministration of fluconazole with RIF is permitted in the higher induction dose cohorts (1600 mg and 2000 mg daily), however, because the impact of any drug-drug interaction (i.e., the extent to which RIF will reduce fluconazole concentrations) is expected to be lessened at these doses. Medications that are prohibited from coadministration with fluconazole are listed in the A5225/HiFLAC Manual of Operations (MOPS) as are those that may be administered with caution.

Additional information can be obtained from the latest fluconazole package insert.

Considerations Regarding Participant Follow Up

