6.2.4 Premature Treatment or Study Discontinuation

Confirmatory HIV Test/Qualifying CSF culture

If **any of the following is true in the given time frame, then** the participant will be discontinued from study treatment, followed for up to 2 weeks, and then discontinued from the study**:**

- the confirmatory HIV test is negative
- the qualifying CSF culture is negative after 2 weeks of incubation
- **a confirmatory CSF antigen titer is negative by Day 5 AND no positive result from the qualifying CSF culture is obtained through Day 4**
- a study entry quantitative culture was required but not performed

In such cases, the participant will be treated as deemed appropriate by his/her primary physician. These participants should complete the evaluations in the Premature Treatment or Study Discontinuation column in the SoE at the time of treatment discontinuation and again approximately 2 weeks later, for study discontinuation; no fluconazole trough PK sample should be collected at these participants’ study discontinuation visit.

Premature Treatment Discontinuation

All participants who prematurely discontinue study treatment (see section 8.1) at any time during the study should complete the Premature Treatment or Study Discontinuation evaluations (per the SoE) within one week after treatment discontinuation. With the exception of participants randomized to ampho B who prematurely discontinue ampho B in Step 1 and who are eligible to register to Step 2, participants who prematurely discontinue study treatment will remain on the step they are on at the time of treatment discontinuation (without registering to subsequent steps) and will continue to be followed on study, off treatment per the SoE, except as noted in sections 6.3.22 and 6.3.24.

Premature Study Discontinuation

Participants who discontinue the study prematurely (see section 8.2) should complete the Premature Treatment or Study Discontinuation evaluations (per the SOE) at the time of study discontinuation.

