6.3.6 ART (Initiation and Modification)

All modifications to ART must be recorded on the CRF. Modifications include initiation as well as any changes in dose or formulation, interruptions of 2 or more consecutive days, or discontinuations for any reason.

Although initiation of ART prior to week 4 is discouraged for participants taking high dose fluconazole, participants who initiate ART that does not contain NVP prior to Step 3 may remain on study. Participants who initiate NVP while taking high dose fluconazole (ie, at a dose higher than 400 mg daily) must be discontinued from study treatment.

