### 9.2 Outcome Measures

9.2.1 Primary Outcomes

9.2.1.1 Discontinuation of **study-provided** fluconazole or ampho B, including precipitating and surrounding adverse events.

9.2.1.2 Qualitative and quantitative CSF culture results at entry, week 2, and when conducted thereafter.

9.2.1.3 Survival.

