### 9.5 Analysis

9.5.1 Stage 1

Dose escalation is based on DLT and the decision rules as outlined above. As noted above, between-dose comparisons to select the fluconazole dose(s) to carry forward will largely be descriptive and not formally powered as all information will be factored into this decision.

9.5.2 Stage 2

In this pilot, we intend to combine the data over both Stages for the ampho B-based cohorts and for fluconazole doses that are tested in Stage 2. As noted above, only the confidence interval around the observed DLT rate in each dose will be adjusted for the dose escalation scheme. Analyses will employ appropriate methods such as Fisher’s exact test to compare dichotomous outcomes (e.g., Grades 3 and 4 events; CSF clearance before week 10) between doses or drugs, and t-tests or Wilcoxon tests to compare continuous covariates between two groups (or ANOVA or Kruskall-Wallis tests if three groups including ampho B). In the event all three fluconazole doses are evaluated in Stage 2, tests for trend such as ANCOVA, Cochran-Armitage and Jonckheere-Terpstra tests will be performed. Survival and other measures of time-to-event from study entry will be summarized with Kaplan-Meier estimates and, where appropriate, tested with log rank tests and possibly proportional hazards regression. The duration of the initial hospitalization will need to consider the duration of hospitalization preceding study entry. The focused neurological exam will be analyzed both on an item-by-item basis and also as a summary measure using methods such as mixed models analysis of variance or GEE that accommodate missing data and changing covariates.

The content and schedule of reports to be available to the core team, the SMC, and the full team will be detailed in the Study Monitoring Plan that will be developed prior to the opening of accrual to the study.

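### Starting nevirapine on more than 400 mg fluconazole stops treatment only under 6.3.6 but ends study participation under 8.2, which would censor survival mostly in the fluconazole arms

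*Protocol*

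**What the plan says.** Five parts of the protocol bear on a participant who starts nevirapine (NVP) while taking more than 400 mg fluconazole daily.

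- Section 2.1.1, drug-drug interactions: "coadministration of NVP and fluconazole at fluconazole doses > 400 mg daily is prohibited in A5225/HiFLAC".
- Section 6.3.6: "Participants who initiate NVP while taking high dose fluconazole (ie, at a dose higher than 400 mg daily) must be discontinued from study treatment". Leaving the study is not ordered.
- Section 8.1 (treatment discontinuation): "Requirement for prohibited concomitant medications (see current A5225/HiFLAC MOPS"). Given 2.1.1, this line covers the event.
- Section 6.2.4: participants who stop treatment early "will continue to be followed on study, off treatment per the SoE". Those who leave the study have "evaluations (per the SOE) at the time of study discontinuation", and nothing is stated after that.
- Section 8.2 (study discontinuation): "Initiation of NVP prior to fluconazole dose reduction to ≤ 400 mg daily".

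Section 9.2.1 lists "9.2.1.3 Survival" among the primary outcomes. Under 9.5.2, "Survival and other measures of time-to-event from study entry will be summarized with Kaplan-Meier estimates".

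**The concern.** Two sites could each follow the text faithfully and treat the same participant differently. One would follow the participant off treatment to week 24, and the other would withdraw the participant at once.

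The second course matters for the analysis. Starting NVP happens after randomisation, and the arms differ in how long it can trigger 8.2. Withdrawal ends the survival record at that point. Kaplan-Meier estimation then assumes that those withdrawn have the same later risk as those who stay. Section 2.2 gives reason to doubt this, since it describes starting NVP-based ART during fluconazole treatment of cryptococcal meningitis as possibly dangerous.

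The rule also runs against the protocol's general approach. Section 3.0 encourages those who stop treatment to stay on study, section 6.3.14 lets women who become pregnant remain off treatment, and section 2.1.1 warns that losses to follow-up can hide real treatment differences.

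**Working it through.** The protocol states no figure on this point, so there is none to reproduce. The check sets the texts side by side and then looks at exposure to the rule and at the cost of each loss.

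**1. The texts.** Section 6.2.4 has its own list of participants who stop treatment and then leave the study after about two weeks: negative HIV confirmation, negative qualifying culture, unconfirmed meningitis, and a required entry culture not done. Starting NVP is not on it. By 6.3.6, 8.1 and 6.2.4 together the participant stays on study; by 8.2 the participant leaves.

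**2. Who can trigger 8.2.** Scheduled weeks above 400 mg through week 10:

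- Fluconazole arms: L weeks of induction, with L from 4 to 10 (Schema). Participants on rifampin then take 600 mg until week 10.
- Ampho B arm, usual path: 400 mg from about week 2, so 0 weeks above 400 mg.
- Ampho B arm, exceptions: Step 2 after intolerance (800 mg or the local maximum) and rifampin in Step 3 (600 mg).

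Two shares are not given and are assumed. The share s of the ampho B arm entering Step 2 is taken as 0 to 34%; the top is the rate of any ampho B modification in the Peruvian study cited in 2.1.2, which is wider than intolerance leading to Step 2. The share r on rifampin is taken as 0 to 30%. Step 2 is assumed to start at about week 1, to be above 400 mg, and to end at week L.

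Fluconazole: F = L + r(10 − L)

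Ampho B: A = s[(L − 1) + r(10 − L)] + (1 − s) × 8r

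Fluconazole share of at-risk weeks: 3F/(3F + A) at 3:1 allocation, or F/(F + A) for 48 vs 48.

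| s | r | L | F | A | 3:1 | 48 vs 48 |
|---|---|---|---|---|---|---|
| 0 | 0 | 4 | 4.0 | 0 | 100% | 100% |
| 0.10 | 0 | 4 | 4.0 | 0.30 | 98% | 93% |
| 0.20 | 0 | 4 | 4.0 | 0.60 | 95% | 87% |
| 0.34 | 0.30 | 4 | 5.8 | 3.22 | 84% | 64% |
| 0.34 | 0.30 | 10 | 10.0 | 4.64 | 87% | 68% |

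The table leaves out locally supplied fluconazole above 400 mg given with ampho B. Adding two such weeks for every ampho B participant to the fourth row gives A = 5.22. The shares are then 17.4/22.62 = 77% and 5.8/11.02 = 53%, still more than half.

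**3. Cost of each loss.** Take a group of n = 48 (the target in 9.3.2) with x participants lost and survival S among the rest. True survival then lies between S(48 − x)/48 and [S(48 − x) + x]/48, a width of x/48 whatever S is.

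- x = 1: 1/48 = 2.1 points.
- x = 3: 3/48 = 6.3 points (with S = 75%, from 70.3% to 76.6%).
- x = 5: 5/48 = 10.4 points (with S = 75%, from 67.2% to 77.6%).

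The values of x and S are illustrations; the protocol gives no expected number. The width is an outer bound on what is unknown, not an estimate of bias.

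**The case against.** The strongest reply is that the sections can be read together. The sentence in 6.3.6 just before the quoted one says that those starting ART without NVP may stay on study, which suggests that NVP starters may not. Section 6.2.4 ties follow-up to 8.1 and withdrawal to 8.2, and only 8.2 names NVP. The contrast adds ambiguity but does not resolve it: the operative instruction in 6.3.6 names treatment only, and the prohibited-medication line in 8.1 points the same way.

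The second reply is that the event should be rare. The combination is prohibited, sites are advised to find alternatives to NVP, efavirenz is allowed from week 4 at any fluconazole dose, ART before week 4 is discouraged on high-dose fluconazole, and 9.3 recommends waiting for Step 3 or 4. This stands. So does the point that sampling error is larger than the effect of a few losses: at an illustrative 28% mortality, the standard error of a 48 vs 48 difference is √(2 × 0.28 × 0.72/48), about 9 points. The week 2 culture outcome is largely untouched, and for culture negativity 9.3.2 already counts early discontinuation as failure. Survival has no such rule.

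A reader might go further and infer three things that the protocol does not support.

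- *That 8.2 removes almost only fluconazole participants from the survival outcome.* Step 2 and rifampin participants in the ampho B arm can trigger it too, and Kaplan-Meier estimation keeps everyone's time before withdrawal.
- *That it favours fluconazole by a calculable amount, given the 82% mortality quoted in 2.2.* That figure concerns ART begun within 72 hours, compared with ART begun after 10 weeks on the same NVP-based drugs. The text gives no fluconazole dose, and the printed fraction 23/26 is 88%, not 82%. It cannot be carried over to NVP started later on high-dose fluconazole.
- *That it undermines the 10-week survival hypothesis.* Hypothesis 1.1.2.2 compares fluconazole doses, and the rule applies to all of them over the same 4 to 10 weeks.

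**Conclusion.** The contradiction is real: 6.3.6, 8.1 and 6.2.4 lead to continued follow-up, and 8.2 ends it. If 8.2 is followed, survival is censored after a post-randomisation event, mostly in the fluconazole arms. That imbalance follows from the dosing schedule and holds across the assumed Step 2 and rifampin shares, though at-risk weeks are not a forecast of events. Section 2.2 makes informative censoring plausible but does not establish it. The number affected is unknown and probably small, and neither the size nor the direction of a bias can be derived. What can be stated is the cost per loss: about 2.1 points on the best/worst-case survival range for each participant out of 48. The case for change rests on an avoidable loss of primary-outcome data and on inconsistent handling between sites.

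**What to change.** Reconcile 6.2.4, 6.3.6, 8.1 and 8.2 so that they give one instruction for this event. The treatment rule is for the protocol team to settle, and no view on it is taken here. Whatever treatment rule is kept, state that the event does not by itself end follow-up: take it off the study-discontinuation list, continue at least vital-status follow-up to week 24 (subject to consent), and analyse survival as randomised.

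The cost is a short text change, mainly one line in 8.2, and a few extra visits or vital-status contacts.

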## 1.0 HYPOTHESES AND STUDY OBJECTIVES

### 1.1 Hypotheses

1.1.1 Fluconazole alone at a dose of 1200, 1600, and/or 2000 mg/day will be well tolerated and safe in participants presenting with HIV-associated CM.

1.1.2 Increasing doses of fluconazole will have increasing efficacy, as follows:

1.1.2.1 Increasing microbiological (fungicidal) efficacy as measured by the mean change between dosing groups in log10 concentration of cryptococci in CSF between baseline and week 2.

1.1.2.2 Increasing clinical efficacy as measured by survival at 10 weeks.

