Missing data elements, particularly those required to assess clinical outcomes, potentially confound interpretation of results. In a double-blind multicenter trial, patients with a first episode of AIDS-associated CM were randomly assigned to treatment with higher-dose ampho B (0.7mg/kg per day) with or without flucytosine (100 mg/kg per day) for 2 weeks, followed by8 weeks of treatment with itraconazole (400 mg per day)or fluconazole (400 mg per day). Treatment was consideredsuccessful if CSF cultures were negative at2 and 10 weeks or if the patient was clinically stable at 2 weeks and asymptomatic at 10 weeks [van der Horst 1997]. An example of distortions produced by missing data is found in the analysis of this trial. A missing CSF culture was deemed positive and the patient was assigned as failing study therapy (Table 2-3). This assumption may have significantly overestimated the incidence of failure. Thus, losses to follow up and failure to collect critical data have probably inflated incidence of failure in past studies and may obscure clinically meaningful differences in treatment outcomes in comparative studies. Therefore, we will attempt to ensure that sites are adequately prepared to conduct this trial and that necessary training is provided.

Table 2-3: Clinical Failure [van der Horst]

|  | Week 2 | | Week 10 | |
| --- | --- | --- | --- | --- |
| Treatment | AmB+5FC | AmB alone | fluconazole | itraconazole |
| Subjects | N= 202 | N= 179 | N= 151 | N= 155 |
| Success (CSF negative) | 122 (60%) | 91 (51%) | 109 (72%) | 93 (60%) |
| Failure | 80 (40%) | 88 (49%) | 42 (28%) | 62 (40%) |
| CSF culture positive | 47 (59%) | 55 (62%) | 3 (7%) | 8 (13%) |
| No CSF sample | 33 (41%) | 33 (38%) | 39 (93%) | 54 (87%) |

Before implementing A5225/HiFLAC, potential sites will be required to document their ability to initiate the study, enroll adequate numbers of participants, conduct clinical investigations according to good clinical practice, follow the protocol outline as specified, and complete the study procedures [lumbar punctures (LP) and CSF cultures]. During the conduct of the study, sites will be asked to periodically provide the team with documentation of their practices in response to issue-specific inquiries. Submission of a revised A5225/HiFLAC SIP may be required. Collaboration among ACTG international sites in this phase I/II clinical trial should prepare them for the larger phase III trial that will probably follow (see below).

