6.2.2 On-Study Evaluations

Entry

On-study evaluations are performed only after a participant is enrolled into the study. However, the following evaluations do not need to be repeated at entry if performed within 72 hours prior to entry: CD4 cell count, plasma HIV-1 RNA, LP with opening pressure recorded, CSF cryptococcal antigen test, CSF cultures initiated (quantitative and qualitative), CSF analyses, and stored CSF sample. Storage of a cryptococcal isolate from CSF collected at screening or entry is sufficient.

Participants must begin study-assigned treatment within 72 hours after entry, however, initiation of study-assigned treatment within 24 hours after entry is strongly encouraged.

Post- Entry

The visit schedule through day 7 should be based on the first day of treatment (day 1 = first day after first dose of fluconazole or ampho B-based regimen), not solely on the date of enrollment. The visits listed for Days 4 through 7 should be completed ± 1 day of those time points as indicated in the SoE, section 6.1.2 and 6.1.3.

The week 2 visit should occur on day 14, but may be completed 12-17 days after initiation of study treatment.

The weeks 4-10 visits should occur on the week noted in the SoE, but may be completed ± 3 days as indicated in the SoE, sections 6.1.2 and 6.1.3. The week 24 visit may be completed ±7 days of that week, as indicated in sections 6.1.2 and 6.1.3. Note that for participants whose previous CSF culture was positive, at least 14 days must elapse between visits.

Step 1 (Induction)

Participants are expected to remain on Step 1 from 2 to 10 weeks depending on the treatment to which they are randomized and their response to that treatment. Participants randomized to ampho B will register to Step 3 after approximately 2 weeks of ampho B treatment. Some participants taking ampho B may register to Step 2 (see below) before entering Step 3.

Participants randomized to fluconazole will remain in Step 1 until week 10 or until a CSF culture is negative, whichever is earlier.

Step 2 (Induction Following Amphotericin B Deoxycholate Intolerance)

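### Section 8.2 ends study follow-up after three consecutive missed visits with no later vital-status check, which risks informative censoring of survival, a primary outcome

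*Protocol*

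**What the plan says.** Protocol section 8.2 (Study Discontinuation) includes "Failure by the participant to attend three consecutive clinic visits". The item stands there, not in section 8.1, which deals with stopping treatment. A participant's own request to withdraw is a separate item in 8.2, so the attendance rule reaches people who have not withdrawn.

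The schedules in sections 6.1.2 and 6.1.3 place visits after entry on days 1, 4 and 7, then at weeks 2, 4, 6, 8, 10 and 24. Section 6.2.2 gives the early windows: "The visits listed for Days 4 through 7 should be completed ± 1 day of those time points", and "The week 2 visit should occur on day 14, but may be completed 12-17 days after initiation of study treatment".

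Section 6.2.4 treats two kinds of exit differently. Those who stop treatment early remain in follow-up. Those who leave the study "should complete the Premature Treatment or Study Discontinuation evaluations (per the SOE) at the time of study discontinuation", and nothing after that is stated.

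Section 9.2.1 names survival as a primary outcome ("9.2.1.3 Survival"). The hypotheses in section 1.1 include "Increasing clinical efficacy as measured by survival at 10 weeks", and section 1.3.3 adds time to death by cohort. For the analysis, section 9.5.2 states: "Survival and other measures of time-to-event from study entry will be summarized with Kaplan-Meier estimates", with log-rank tests where appropriate.

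**The concern.** Kaplan-Meier and log-rank methods assume that participants who leave have the same later risk of death as those who stay. Absence from three visits in a row is poor ground for that assumption in this disease: section 9.3.1 expects up to 15% very early mortality in any cohort, and an absent participant may be too ill to attend or already dead. If the study closes the participant's record at that point and does not ask later whether he or she is alive, some deaths will never reach the database. A statistical analysis plan can define how such participants are censored, but it cannot supply deaths that the protocol did not collect. At stake is the level of mortality in each group. Comparisons between groups would also be affected if attendance differs between them.

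**Working it through.** **1. When the rule can be met.** Each run of three consecutive visits in the schedule of events, with the window of the third visit:

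| Visits missed | Rule met by day |
|---|---|
| Days 1, 4, 7 | 6-8 |
| Day 4, day 7, week 2 | 12-17 |
| Day 7, weeks 2, 4 | 25-31 |
| Weeks 2, 4, 6 | 39-45 |
| Weeks 4, 6, 8 | 53-59 |
| Weeks 6, 8, 10 | 67-73 |
| Weeks 8, 10, 24 | 161-175 |

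The first five runs end before the week 10 window opens, so for them the rule acts before the survival time point named in the hypotheses. The sixth ends at week 10 and takes away only the week 24 visit. The last takes away nothing.

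**2. What is collected afterwards.** After treatment discontinuation, follow-up continues (section 6.2.4), and section 3.0 encourages a return at week 24. After study discontinuation there is one set of evaluations at exit, which an absent participant is unlikely to complete. The only contact after study exit that the protocol describes is for pregnancy outcomes (section 7.7). None is described for vital status.

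**3. Size.** The protocol gives no loss rate, expected number of deaths or power for survival, so there is no planned figure to reproduce. An illustration needs three inputs:

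- Mortality among those retained, m_ret = 25%. This is the 10-week figure from one South African study of ampho B plus flucytosine described in section 2.1.2 (16 of 64 died).
- Proportion lost, L = 5%, 10% or 15% (assumption).
- Mortality among the lost, m_lost = 25%, 50% or 75% (assumption).

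True mortality = (1 - L) × m_ret + L × m_lost. If the estimate is close to m_ret, the understatement is L × (m_lost - m_ret).

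| L | m_lost 25% | m_lost 50% | m_lost 75% |
|---|---|---|---|
| 5% | 0 | 0.05 × 25 = 1.25 | 0.05 × 50 = 2.5 |
| 10% | 0 | 0.10 × 25 = 2.5 | 0.10 × 50 = 5.0 |
| 15% | 0 | 0.15 × 25 = 3.75 | 0.15 × 50 = 7.5 |

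Entries are percentage points. Where the lost die more often than the retained, the range is 1.25 to 7.5, or about 1-8 points. This is a simple mixture of proportions. A Kaplan-Meier estimate also uses the time at risk that the lost contribute before exit, so the figures are approximate.

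**4. Bounds without assuming mortality in the lost.** Section 9.3.2 aims for 48 per group over both stages. With 5 lost and 11 deaths in the 43 retained, observed mortality is 11/43 = 25.6%. It could truly be anything from 11/48 = 22.9% (all lost alive) to 16/48 = 33.3% (all lost dead). With 7 lost and 10 deaths in 41, observed mortality is 24.4% and the bounds are 10/48 = 20.8% and 17/48 = 35.4%. Each unrecorded death moves group mortality by 1/48, about 2 points.

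**The case against.** The strongest reply is that absence, not the rule, causes most of the loss. By the time the rule acts, three visits have already been missed, and someone who never returns leaves the same gap with or without it. This largely stands. Deleting the line alone would recover only those who would have come back; the larger gain comes from active tracing, which the protocol does not provide.

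It also stands that early triggering may be uncommon. Ampho B is given intravenously under close observation for about two weeks, and study staff are expected to work with hospital staff while participants are inpatients. Missing day 4, day 7 and week 2 is plausible mainly for a participant on oral fluconazole who is discharged early.

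The consequences are limited too. This is a pilot, the primary efficacy measure is the quantitative CSF culture, survival carries no power statement, and between-dose choices after Stage 1 are largely descriptive. Culture negativity already counts early discontinuation or death as failure.

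Three stronger readings are tempting, and the documents do not support them:

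- A reader might take the week 10 missing-sample counts in Table 2-3 (39 of 151 and 54 of 155) as loss rates. They count absent CSF samples, not missed visits or unknown vital status, and say nothing about how often this rule would operate.
- A reader might cite the remark in section 2.1.1 that "losses to follow up and failure to collect critical data have probably inflated incidence of failure in past studies" as the protocol's own warning of understated mortality. It concerns missing cultures scored as positive, which pushes in the other direction. Only its general point, that losses can obscure differences, carries over.
- A reader might infer that the bias falls on a particular arm. No difference in attendance between arms is documented.

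**Conclusion.** The point holds as a design weakness that is cheap to remedy; it is not a contradiction or a proven bias. The protocol ends study participation on a ground that is plausibly related to death, can do so by day 12-17 or earlier, and states no later check of vital status although survival is a primary outcome. That the censoring would be informative is an inference from the disease and the analysis method; the protocol states no censoring rule for survival. The direction, understated mortality, depends on absent participants dying more often than those retained. The size cannot be fixed from the documents: about 1-8 points under the assumed losses and mortality, and zero if mortality is equal. The part that later analysis cannot repair is the missing information on who died.

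**What to change.** 1. In section 8.2, reword the attendance item so that three consecutive missed visits stop scheduled visit procedures only and do not end participation in the study.
2. In section 6.2.4, require vital status, with date of death where applicable, at week 10 and week 24 for all randomised participants, by telephone, family contact or hospital record, unless consent to contact is withdrawn.
3. In section 9.5.2, state that the survival analysis uses these data, and report by group the number whose vital status remains unknown at each time point.

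The cost is a wording change in three sections and a few extra contacts per absent participant. No treatment or visit schedule changes. Section 9.5.2 pools the two stages, so if Stage 1 follow-up is already closed, the report should say which stage's participants had vital status traced in this way.
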